# 2.0 PROTOCOL SUMMARY

Title: Post-acute Structured Exercise Following Sport Concussion: a Randomized Controlled Study

Overview: This study will investigate the effect of structured, structured aerobic exercise protocol (SAEP) compared to usual care on clinical recovery from sport-related concussion (SRC) within the post-acute phase of injury. Participants will be randomized into one of two groups: (1) Supervised Exercise Group: participants will complete a total of eight exercise sessions over the course of 11 days, starting at Day 3 post-injury (two sessions (first and mid-point) will be done in the lab, and the remained will be home-based sessions); (2) Usual Care Group: individuals will undergo a period of physical rest and standard care. For the purposes of this study, "rest" will be defined as the avoidance of any activities beyond those of daily living, including participation in sport and physical activity.

Objectives: *Primary:* To investigate the utility of an SAEP initiated in the sub-acute phase after SRC in reducing post-concussion symptoms and the time to medical clearance, compared to usual care. *Secondary:* To determine the effect of an SAEP in concussed subjects on ANS function, blood biomarkers, and cognition

Outcome Measures: *Primary*: post-concussion symptom scores and days to medical clearance; *Secondary:* a) cardiovascular responses [heart rate variability (HRV) and blood pressure variability (BPV)], b) cognitive performance, and c) neuroinjury/neuroreparative blood biomarkers (BDNF, glial fibrillary acidic protein [GFAP], peroxiredoxin [PRDX]-6, monocyte chemoattractant protein [MCP]-1), and catecholamines (norepinephrine [NE] and epinephrine [Epi]).

Endpoints: *Primary:* Days to asymptomatic status and days to medical clearance *Secondary:* Cardiovascular, cognitive, and neuroinjury markers at Day 90 post-injury.

Population:

Age: 13-25 years, Sex: All

Inclusion Criteria:

Diagnosed with SRC by a physician at the David L. MacIntosh Sport Medicine Clinic

Able to speak and understand English

Exclusion Criteria:

Have had a previous concussion within two weeks of the presenting SRC

Have any co-morbid injuries (i.e. musculoskeletal/soft-tissue injuries, vestibular disorders)

Have a pre-existing heart condition

Have any uncontrolled seizure disorders or a history of medical or neurological conditions that affects cognitive functioning

Number of Sites: 1

Study Duration: 36 months

Participant Duration: 90 days

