***Hypothesis 1 – Clinical recovery:***

Individuals in the SAEP will have lower symptom scores and faster return to asymptomatic status, leading to shorter clinical recovery times compared to those in usual care group.

**Specific Aim 2:** To determine the effect of an SAEP in concussed subjects on ANS function, blood biomarkers, and cognition.

***Hypothesis 2a*** – Cardiovascular responses:

Compared to the SAEP, the usual of care group will display lower HRV and BPV at days 14, 21, and 28 post-SRC.

***Hypothesis 2b:*** *- Peripheral blood biomarkers:*

As compared to the usual of care group, the SAEP group will display higher peripheral concentrations of neuroreparative indices BDNF and PRDX-6, lower concentrations of the CNS-injury analogue GFAP, lower concentrations of the inflammatory marker MCP-1, and lower resting peripheral catecholamine levels.

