# 9.0 STUDY DESIGN

**Design:** A single blinded, randomized, controlled trial with 7-, 14-, 21-, 28-, and 90-day follow-up visits.

**Setting:** David L. MacIntosh Sport Medicine Clinic at the University of Toronto.

**Main Outcome Measures**: *Primary outcome measures*: post-concussion symptom scores and days to medical clearance; *Secondary outcome measures:* a) cardiovascular responses [heart rate variability (HRV) and blood pressure variability (BPV)], b) cognitive performance, and c) neuroinjury/neuroreparative blood biomarkers (BDNF, glial fibrillary acidic protein [GFAP], peroxiredoxin [PRDX]-6, monocyte chemoattractant protein [MCP]-1), and catecholamines (norepinephrine [NE] and epinephrine [Epi]).

**Intervention**: Structured Aerobic Exercise Protocol or Usual Care.

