## 9.5 Structured Aerobic Exercise Protocol (SAEP)

The proposed exercise protocol will consist of 8 sessions, proceeding in a stepwise fashion with respect to duration and intensity over the course of 11 days, with two consecutive sessions proceeded by one day of rest. A fixed wattage stationary bike (Velotron Dyndafit Pro, manufactured by Racermate Inc., Seattle, WA, USA) will be used for all exercise sessions. The use of a stationary bike will ensure head and neck stability, avoiding any unwanted accelerations of the head (cf. treadmill). Finally, the bike will be connected to an interactive heart rate monitor (Polar®, Kempele, Finland), allowing the research team to control the wattage of the bike for each individual subject.

The first session of the AE protocol will take place on the Day 3 post-injury, and will comprise 15 minutes of steady-state exercise at 60% of the participant’s age-predicted maximal HR (apHR), plus a warm-up and cool-down period (25 minutes total). The participant’s symptoms will be monitored before, during, and after exercise. If the participant’s symptoms are not exacerbated, they will proceed to the next exercise level, consisting of 20 minutes of steady-state exercise, at 60% of apHR, plus warm-up and cool-down (30 minutes total). Please see **Table 1.** below for a detailed summary of the exercise protocol. Participants’ HR and BP will be recorded before and after each exercise session. Symptoms will also be recorded before and after each exercise session using the PCSS, and a trained kinesiologist will monitor symptoms throughout the exercise session. A prepared script to monitor symptoms has been developed to ensure standardization. If participants in the exercise group achieve asymptomatic status at the two weeks post-injury, they will continue to progress through the AE intervention until they complete all eight sessions, and will also begin progressing through the existing clinical RTP guidelines.

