# 14.0 DESCRIPTION OF STATISTICAL METHODS

## 14.1 Analysis of Primary Endpoints

We will statistically evaluate time to medical clearance between the standard of care and AE intervention groups by Cox regression (or proportional hazards regression). This approach allows one to control for the effect of several variables (i.e., sex/gender, age, initial PCSS), while evaluating a single outcome measure. Furthermore, we have the ability account for censor subjects who are removed from the study due to exercise-induced symptom exacerbation or attrition.

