## 14.2 Analysis of Secondary Endpoints

Furthermore, A mixed model ANOVA will be used to evaluate possible differences in symptoms, HRV, BPV, cognitive performance and blood biomarkers between the standard of care group and AE intervention group (between group analysis) across 6 time points; 7, 14, 21, 28, and 90 days post-SRC (within group analysis). If the data fails the required normality assumption, the appropriate transformation will be performed on all data. We expect approximately 40% females in our study sample, allowing for differential responses between males and females. We will perform separate Kaplan Meier analyses in males and females on time to medical clearance between the standard of care and AE intervention groups. Likewise, we will perform separate mixed model ANOVA analyses in males and females to evaluate differences between AE intervention and standard care groups for all aforementioned secondary measures.

Regarding blood biomarker analysis, each individual biomarker will only be included for statistical quantitation if they fall within the lower and upper limits of quantitation (LLOQ and ULOQ, respectively) as delineated by the manufacturer. All samples will be run in duplicate, and excluded if the coefficient of variance (CV) between duplicate samples is > 25%. Furthermore, mean statistical analysis will only be performed on biomarkers that have quantifiable samples in > 50%, in all groups in question. A quantifiable sample is 1) within the manufacturers quantitative range, and 2) displays a CV between duplicates of < 25%. In instances where one or both groups contain <50% quantifiable samples, differences between these groups will be evaluated by χ^2^.

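### The protocol contradicts itself on the primary endpoint: three outcomes are called primary in different places, and only time to medical clearance has a primary analysis and a sample size

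*Protocol*

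**What the plan says.** **Primary endpoint**

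- Section 2.0 (Outcome Measures) and Section 9.0 (Main Outcome Measures) list as primary "post-concussion symptom scores and days to medical clearance".
- Section 2.0 (Endpoints), a few lines below its own outcome list, gives the primary endpoints as "Days to asymptomatic status and days to medical clearance".
- Section 8.0, Hypothesis 1, runs all of these together: "lower symptom scores and faster return to asymptomatic status, leading to shorter clinical recovery times". It does not say which of them decides the result.
- Section 13.0 sizes the trial on time to clearance (43 days reduced to 36, SD 20) at significance level 0.05.
- Section 14.1, the primary analysis section, covers one variable: "We will statistically evaluate time to medical clearance between the standard of care and AE intervention groups by Cox regression".
- Section 14.2, the secondary analysis section, takes in symptoms: "A mixed model ANOVA will be used to evaluate possible differences in symptoms, HRV, BPV, cognitive performance and blood biomarkers".
- Section 14 contains no analysis of time to asymptomatic status. Section 9.1 defines only the symptomatic state (PCSS of five or more), for eligibility.

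**Symptom recording**

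- Both arms have assessments on Days 7, 14, 21, 28 and 90 (Section 9.0).
- The exercise arm has more: "Symptoms will also be recorded before and after each exercise session using the PCSS" (Section 9.5). Table 1 puts the eight sessions on Days 3, 4, 6, 7, 9, 10, 12 and 13.

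**Secondary endpoints**

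- Section 2.0 (Endpoints): "Cardiovascular, cognitive, and neuroinjury markers at Day 90 post-injury".
- Section 8.0, Hypothesis 2a, says that the usual care group "will display lower HRV and BPV at days 14, 21, and 28 post-SRC". Hypothesis 2c names the same three days for cognition.

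**The concern.** The primary endpoint fixes what the trial can claim. Here one variable (symptom scores) is primary in the outcome lists and secondary in the analysis section. Another (time to asymptomatic status) is primary in the endpoint line and is never analysed. A third (clearance) is primary throughout and has used the whole 0.05 in the sample size. A reader of the results could not tell from the protocol whether a significant symptom result with a null clearance result, or the reverse, makes the trial positive. If that choice is left until the data are seen, the 5% error rate is not protected.

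Two related gaps follow. First, nothing says which symptom records date the asymptomatic endpoint, although one arm is checked far more often during the first two weeks. Second, the secondary endpoints are fixed at Day 90 in one place and at Days 14, 21 and 28 in another.

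**Working it through.** **1. The statements side by side**

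| Outcome | 2.0 and 9.0 outcome lists | 2.0 Endpoints line | 13.0 sample size | 14.1 primary analysis | 14.2 secondary analysis |
|---|---|---|---|---|---|
| Time to clearance | primary | primary | yes | yes (Cox) | by-sex Kaplan-Meier only |
| Symptom scores | primary | not listed | no | no | yes (mixed model ANOVA) |
| Time to asymptomatic status | not listed | primary | no | no | no |

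Three variables are called primary somewhere. Two have a planned test. One has a primary analysis.

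**2. The plan's own figure**

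Section 13.0 states 53 per group for a 7-day difference with SD 20 at 0.05. With n = 2(z₁₋α/₂ + z₁₋β)²(SD/δ)², two-sided 0.05 and an assumed 80% power, n = 2 × (1.960 + 0.842)² × (20/7)² ≈ 128.1, so 129 per group. The stated 53 is not reproduced from those inputs. That is a separate defect. What matters here is that the calculation concerns clearance alone and spends all of the 0.05 on it.

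**3. False-positive rate under each reading**

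Assumptions: each outcome is tested two-sided at 0.05 (Section 13.0 does not state sidedness), the symptom ANOVA is counted as one test, and there is no true effect on either outcome.

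- Section 14.1 governs, so there is one primary test: 5%.
- Both outcomes must succeed: at most 5%.
- Either outcome suffices, tests independent: 1 − 0.95² = 0.0975, or 9.75%.
- Either outcome suffices, tests correlated (simulated bivariate normal statistics, 2,000,000 draws):

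| Assumed correlation | 0.3 | 0.5 | 0.7 | 0.9 |
|---|---|---|---|---|
| At least one false positive | 9.5% | 9.1% | 8.3% | 7.0% |

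The protocol gives no correlation, so the whole range is shown.

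**4. What session scores would do to time to asymptomatic status**

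Suppose that the date is the first check after symptoms resolve, that session scores count as checks, and that there are no other visits. Within an interval of length L between checks, a uniformly distributed resolution time waits L/2 on average. For resolution uniform on Days 3 to 14:

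- Usual care (checks at 7 and 14; intervals 4 and 7): (4² + 7²)/(2 × 11) = 65/22 = 2.95 days.
- Exercise (checks at 4, 6, 7, 9, 10, 12, 13 and 14; intervals 1, 2, 1, 2, 1, 2, 1, 1): 17/22 = 0.77 days.
- Difference: 48/22 = 2.18 days.

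After Day 14 the schedules are the same and the difference is zero. The average artefact is therefore 2.18 × p, where p is the share resolving by Day 14: 0 at p = 0, 1.09 days at p = 0.5 and 2.18 days at p = 1. The protocol gives no value for p.

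**The case against.** The strongest reply is that the protocol does plan one primary test. Section 14.1 names clearance, Section 13.0 sizes the trial on it, and no sentence says that success on any one listed outcome is enough. The outcome list and the endpoint line can also be partly reconciled by taking symptom scores as the measure and time to asymptomatic status as the endpoint drawn from it. A multiplicity rule may sit in a statistical analysis plan that is not at hand. All of this stands as far as it goes: the missing multiplicity rule is not the finding, and the inflation is conditional. It does not remove the conflict, because on any reading something labelled primary is either analysed as secondary or not analysed. An analysis plan could settle that only by departing from one of the protocol's own statements.

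Three stronger readings are tempting, and the documents do not support them.

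- **Three chances at 0.05.** A reader might infer a 14.3% error rate (1 − 0.95³). The third variable has no planned test, and it would presumably be derived from the symptom scores, so independence is implausible.
- **A comparison biased by construction.** No section says that session scores date the asymptomatic endpoint. Sections 9.2 and 10.0 use session monitoring for exacerbation and termination. Section 9.2 allows asymptomatic status to be reached at any point, while Section 9.5 speaks of it at two weeks, so the source is unspecified. Section 9.6.1 also leaves clinical follow-up to the physician, so usual care may have further checks. Setting 2.18 days against the 7-day target would mix endpoints, since that target is for clearance.
- **Day 90 as the point where differences are least likely.** The planning figures imply that nearly everyone would be cleared by then, but nothing links normalisation of cardiovascular, cognitive or blood markers to clearance. Section 14.2 analyses Day 90 together with the earlier days.

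**Conclusion.** The contradiction is established from the text and needs no assumption: the primary endpoint differs between the outcome lists, the endpoint line and the analysis section, and one named primary has no analysis and no explicit definition. It has to be settled before any confirmatory claim is made.

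The size of the error inflation is conditional. It is 7.0% to 9.75% over the correlations examined (0.9 down to 0) if either tested outcome may carry the trial, and at most 5% if clearance alone governs or both must succeed. The protocol does not say which applies.

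Unequal ascertainment is a risk to close off, not a demonstrated bias. It would arise if session scores were used for dating, and its size depends on the unknown share resolving by Day 14. The secondary time points are inconsistent between Sections 2.0 and 8.0 and need reconciling; no claim is made about which day is more informative.

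**What to change.** **Preferred.** Name time to medical clearance, analysed by Cox regression as in Section 14.1, as the single primary endpoint in Sections 2.0, 8.0, 9.0 and 14. It is the only outcome with both a sample size and a primary analysis. List symptom scores and time to asymptomatic status as secondary. The cost is a wording change, and symptoms lose the primary status that Aim 1 gives them.

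**Alternative.** Keep two primaries, stating whether one or both must succeed and how alpha is allocated, and move the second one's analysis into Section 14.1. An equal split costs sample size: at α = 0.025, a 7-day difference, SD 20 and 80% power, the formula above gives 156 per group against 129 at 0.05. Requiring both to succeed needs no split but lowers the chance of a positive trial.

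**If time to asymptomatic status is kept at either level.** Define it explicitly, give it an analysis, and date it in both arms only from the common assessments (Days 7, 14, 21, 28 and 90), leaving out session PCSS scores. The cost is coarser dating, which calls for an interval-censored analysis. No new data collection is needed.

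**Secondary endpoints.** Reconcile the Day 90 line in Section 2.0 with the Days 14, 21 and 28 of Hypotheses 2a and 2c, and state the time points for the biomarkers, since Hypothesis 2b names none.

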# 5.0 BACKGROUND INFORMATION

Concussions are a significant health concern occurring frequently in athletic setting^11,12^. The literature commonly cites spontaneous recovery within 7-10 days, however, this evidence has been historically limited to sport-related concussions (SRC) among US collegiate and professional athletes^13^. A recent meta-analysis and data from Canadian pediatric emergency departments document significantly longer recovery times, particularly for younger individuals^14,15^. Current medical guidelines advise complete physical and cognitive rest acutely after SRC, followed by gradual re-introduction of activity in a standardized manner^16^. Notably, the most recent Concussion in Sport Consensus Statement highlighted that the exact amount and duration of rest is not yet well defined in the literature and requires further study^16^.

The current standard care after concussion is largely predicated upon experimental animal studies, which have shown a decrease in energy availability in the brain resulting from neurometabolic disruption^17^. From this, it has been speculated that any activity after injury may exacerbate this hypermetabolic state, increase symptoms, and delay recovery^18,19^. However, recent evidence suggests there is no added benefit of rest on symptom recovery after concussion beyond 3 days^18^, and inactivity may contribute to the development of maladies often concomitantly present in concussion sufferers, such as mental health conditions, chronic fatigue, and pain disorders^18^.

A growing body of research has demonstrated that early-onset, graded aerobic exercise (AE) interventions following central nervous system (CNS) injuries such as stroke, whiplash, and low-back pain, can accelerate recovery and improve functional outcomes compared to rest alone^18,20-24^. While the underlying therapeutic mechanisms are unclear, it is thought that exercise may expedite parenchymal tissue regeneration and restore dysregulated autonomic system (ANS) function^3,21,25-31^. In traumatic brain injury (TBI), early AE intervention in animal models has shown improved cognitive recovery and alleviation of symptoms, alongside numerous biological alterations such as increased neurogenesis, decreased apoptosis in the hippocampal regions, enhanced survival of purkinje fibres, and suppression of reactive gliosis^29,32-36^.

While preliminary human investigations using AE interventions after concussion have shown promise, these studies are either retrospectively designed^37^, or have focused on individuals with persistent symptoms (> 3 weeks)^38-40^. Given the promising evidence of the therapeutic potential of AE interventions, and the large percentage of adolescents and young adults at risk for concussion^16,41,42^, the purpose of this study is to examine the effect of a standardized, subacute AE intervention on recovery after SRC compared to usual care. This study will provide meaningful information regarding the utility and optimal implementation of AE intervention after concussion. Findings from these works may inform future usual care procedures post-injury, potentially providing the first known treatment to improve recovery after concussion. Furthermore, as AE is easily implementable and not resource intensive, its use in the treatment of concussion could have widespread impact.

# 6.0 THE NEED FOR A TRIAL

## 6.1 Pathophysiology following SRC

The underlying mechanisms mediating recovery following SRC are not well understood. However, evidence suggests the initial trauma leads to neurometabolic disruption, neuroinflammation, and autonomic nervous system (ANS) dysregulation ^17,43-45^.

After injury, trauma to neuronal tissue, particularly as a result of shearing forces, leads to a cascade of events including microporation of lipid cellular membranes, glutamate release from damaged cells, depletion of intracellular energy, and calcium mediated parenchymal tissue damage^17^. Additionally, the neuroinflammatory response is activated, which can paradoxically lead to the beneficial removal of extracellular glutamate, neurogenesis, angiogenesis and axonal remodeling, but may also facilitate detrimental processes such as the overproduction of cytokines, chemokines, reactive oxygen species (ROS), and the isolation of injured areas of the brain from healthy tissue^46,47^. Consistent with this, employing advanced neuroimaging and peripheral blood biomarker analysis, our group and others have identified evidence of neurometabolic disruption, CNS injury, and inflammation across the spectrum of human TBI^7-10,48-53^. Furthermore, concussion may also cause dysfunction to the central autonomic system (ANS) due to sheer forces form the insult, resulting in subtle structural alterations in brainstem regions responsible for autonomic modulation^19^. Indeed, heart rate variability (HRV) impairments have been observed in mild traumatic brain injury (mTBI) patients ^54^, and our group recently identified a decrease in HRV in athletes post-SRC^3,7-10,48^. Notably, we have also found numerous pathological relationships between sympathetic hyperactivity and secondary injury processes in TBI patients ^7,9^.

## 6.2 Current concussion management

Concussion is a disturbance in brain function caused by direct or indirect force to the head. Therefore, the diagnosis of concussion requires determination of a temporal relationship between an appropriate mechanism of injury and signs and/or symptoms. Most recent management guidelines for mTBI still universally recommend an initial period of rest^55,56^; this is reflected in the consensus statement derived from the 5^th^ international conference on Concussion in 2016, where it is recommended that following a period of rest after injury, patients may be encouraged to become gradually and progressively more active while staying below their cognitive and physical symptom-exacerbation thresholds^16^. Unfortunately, the appropriate intensity, frequency, and duration of activity is unclear. In addition, given that too much activity has been associated with worse outcomes^57^, careful investigation is needed in order to inform future evidence-based guidelines.

